### Safety reporting

The safety profile of chloroquine is well understood and the risks related to chloroquine phosphate/sulphate/hydrochloride are very low, unless the drug is taken in overdose
^28^. Most side effects are infrequent. Adverse reactions (ARs) relating to the cardiovascular system, the central nervous system, the skin, hypoglycaemia, hypersensitivity, gastrointestinal, and retinal toxicity have all been described, though usually after high doses and protracted exposures. The main adverse effect is itching in dark-skinned individuals; Africans are much more commonly affected compared to Asians. Adverse effects will be classified and graded according to the Common Terminology Criteria for Adverse Events (CTCAE) system
^29^. All serious and grade 3 or 4 AEs will be compared between arms and reported by frequency per arm. An independent DMC will oversee the safety of the trial participants.

***Definitions***. The definitions of the principles of International Conference on Harmonization (ICH) Good Clinical Practice (GCP) apply to this trial protocol (see
Table 4).

**Table 4. T4:** International Conference on Harmonization (ICH) Good Clinical Practice (GCP) definitions.

Table	Definition
Adverse event (AE)	Any untoward medical occurrence in a participant or clinical trial subject to whom an investigational medicinal product has been administered including occurrences that are not necessarily caused by or related to that product.
Adverse reaction (AR)	Any untoward and unintended response to an investigational medicinal product related to any dose administered.
Unexpected adverse reaction (UAR)	An AR, the nature or severity of which is not consistent with the information about the investigational medicinal product in question set out in the Summary of Product Characteristics (SPC) for that product.
Serious adverse event (SAE) or serious adverse reaction (SAR) or suspected unexpected serious adverse reaction (SUSAR)	Respectively any AE, AR or UAR that: Results in death Is life-threatening * Requires hospitalisation or prolongation of existing hospitalisation ** Results in persistent or significant disability or incapacity Consists of a congenital anomaly or birth defect Is another important medical condition ***

^*^ The term life-threatening in the definition of a serious event refers to an event in which the participant is at risk of death at the time of the event; it does not refer to an event that hypothetically might cause death if it were more severe, for example, a silent myocardial infarction.

^**^ Hospitalisation is defined as an inparticipant admission, regardless of length of stay, even if the hospitalisation is a precautionary measure for continued observation. Hospitalisations for a pre-existing condition (including elective procedures that have not worsened) do not constitute an SAE.

^***^ Medical judgement should be exercised in deciding whether an AE or AR is serious in other situations. The following should also be considered serious: important AEs or ARs that are not immediately life-threatening or do not result in death or hospitalisation but may jeopardise the subject or may require intervention to prevent one of the other outcomes listed in the definition above.

AEs include:
An exacerbation of a pre-existing illnessAn increase in frequency or intensity of a pre-existing episodic event or conditionContinuous persistent disease or a symptom present at baseline that worsens following administration of the study intervention

ARs include any untoward or unintended response to drugs. Reactions to the trial treatment (chloroquine) or comparator should be reported appropriately.

In the context of this trial AEs do not include:
Medical or surgical procedures; the condition that leads to the procedure is the AEPre-existing disease or a condition present before treatment that does not worsenHospitalisations where no untoward or unintended response has occurred, e.g. elective cosmetic surgery, social admissionsOverdose of medication without signs or symptoms

Death should always be reported as a SAE, regardless of cause.

***Assessment of AEs***. All grade 3 or 4, or SAEs and SARs, whether expected or not, should be recorded in the CRF. Non-serious grade 1 or 2 AEs need not be recorded unless they are thought to be related to the trial treatment or they result in a change or interruption in treatment.

A laboratory abnormality must be recorded as a clinical AE only if it is associated with an intervention. Intervention includes, but is not limited to, discontinuation of a current treatment, dose reduction/delay of a current treatment, or initiation of a specific treatment. In addition, any medically important laboratory abnormality may be reported as an AE at the discretion of the investigator. This would include a laboratory result for which no intervention is needed, but the abnormal value suggests a disease or organ toxicity. Laboratory events will be graded according to CTCAE definitions.

Seriousness

When an AE or AR occurs, the investigator responsible for the care of the participant must first assess whether or not the event is serious using the definition given in
Table 4. If the event is serious and not only related to COVID-19, or is fatal, then an SAE Form must be completed and the OUCRU clinical trials unit (CTU) notified within 24 hours.

Severity or grading of AEs

The severity of all AEs and/or ARs (serious and non-serious) in this trial should be graded using the toxicity gradings in Toxicity grading and management (CTCAE)
^29^.

Causality

The investigator must assess the causality of all serious events or reactions in relation to the trial therapy (chloroquine) using the definitions in
Table 5. There are five categories: unrelated, unlikely, possible, probable, and definitely related. If the causality assessment is unrelated or unlikely to be related, the event is classified as an SAE. If the causality is assessed as possible, probable or definitely related, then the event is classified as an SAR.

**Table 5. T5:** Assigning type of SAE through causality.

Relationship	Description	SAE type
Unrelated	There is no evidence of any causal relationship	Unrelated SAE
Unlikely	There is little evidence to suggest that there is a causal relationship (for example, the event did not occur within a reasonable time after administration of the trial medication). There is another reasonable explanation for the event (for example, the participant’s clinical condition, other concomitant treatment).	Unrelated SAE
Possible	There is some evidence to suggest a causal relationship (for example, because the event occurs within a reasonable time after administration of the trial medication). However, the influence of other factors may have contributed to the event (for example, the participant’s clinical condition, other concomitant treatments).	SAR
Probable	There is evidence to suggest a causal relationship and the influence of other factors is unlikely.	SAR
Definitely	There is clear evidence to suggest a causal relationship and other possible contributing factors can be ruled out.	SAR

SAE, serious adverse event; SAR, serious adverse reaction.

Expectedness

If an AE or AR is not expected with COVID-19 disease or with chloroquine, then it is unexpected. An unexpected adverse reaction (UAR) is one not previously reported in the current Summary of Product Characteristics (SPC) at the time the event occurred, or one that is more frequent or more severe than previously reported. The definition of an UAR is given in
Table 4. If an SAR is assessed as being unexpected, it becomes a suspected unexpected serious adverse reaction (SUSAR).

Investigators should always check the current version of the SPC. Expected toxicities associated with chloroquine are:
Frequency unknown: Abdominal pain; agranulocytosis; alopecia; anxiety; atrioventricular block; bone marrow disorders; confusion; corneal deposits; depression; diarrhoea; eye disorders; gastrointestinal disorder; headache; hearing impairment; hypoglycaemia; hypotension; insomnia; interstitial lung disease; movement disorders; myopathy; nausea; neuromyopathy; neutropenia; personality change; photosensitivity reaction; psychotic disorder; QT interval prolongation; seizure; severe cutaneous adverse reactions (SCARs); skin reactions; thrombocytopenia; tinnitus; tongue protrusion; vision disorders; vomiting.Rare or very rare: Cardiomyopathy; hallucination; hepatitisOverdose: Overdose is difficult to treat and can result in life-threatening features including arrhythmias (which can have a very rapid onset) and convulsions (which can be intractable). Hypoglycaemia can also feature. However, treatment in this study will be directly observed as an in-patient and therefore is extremely unlikely.

***Regulatory reporting***. All SAEs will be reported as soon as possible to the MoH ethics committee. An initial written report of an SAE resulting in death, or that is life threatening, has to be reported urgently within seven working days of the study team becoming aware of the SAE. Other SAEs must be reported within 15 working days of the study team becoming aware of the SAE. Additional medical information of the SAE’s development must be reported in an additional report until the trial participant recovers or stabilizes without further changes expected. The format and content of the initial report should follow the Vietnam MoH EC report template and include all information available at the time of reporting. All SAEs will be reported to OxTREC in the annual review form and to the DMC in accordance to the DMC charter.

***Safety reporting***. An independent DMC will oversee the safety of the trial. A DMC Charter will describe the membership of the DMC, relationships with other committees, terms of reference, decision-making processes, and the approximate timing and frequency of interim analyses (see
*Extended data*
^27^). At the interim analyses, the DMC will receive a report including summaries of mortality, SAEs, grade 3 and 4 AEs, and the time to viral clearance (defined as the time following randomization until the midpoint between the last positive and the first of the negative throat/nose swabs) by treatment arm. The report will be prepared by the study statistician and distributed to all DMC members for review. Based on these data, the committee will make recommendations on the continuation, cessation or amendment of the study.

The DMC will perform a first safety analysis after the first 10 participants from the pilot study have completed the allocated two-week treatment or died. A second and a third interim safety analysis will be performed assessing safety, efficacy and futility, after 60 and 120 participants have completed the allocated two-week treatment or died. Stopping for harm of chloroquine will be considered if a safety issue emerges which is sufficiently large, in the judgement of the DMC, to suggest that continued exposure of participants to the drug is unethical. Early stopping for efficacy is not foreseen, as this is a study with a virological rather than survival endpoint. However, if chloroquine truly appears to have an extraordinary beneficial effect then the DMC will be able to recommend this to the TSC. The DMC will be able to mandate additional safety analyses at any time point they deem fit.

As the dissemination of preliminary summary data could influence the further conduct of the trial and introduce bias, access to interim data and results will be confidential and strictly limited to the involved statistician and the monitoring board and results (except for the recommendation) will not be communicated to the outside and/or clinical investigators involved in the trial. Further reviews will be at the discretion of the DMC. All DMC reports, replies or decisions will be sent to the responsible research ethical committees.

***Protocol violations***. A protocol deviation is any non-compliance with the clinical trial protocol or GCP requirements. If such a deviation results in an impact on patient safety or scientific integrity it becomes a protocol violation. The non-compliance may be either on the part of the participant, the investigator, or the study site staff. Whenever violations occur, corrective actions are to be developed by the site and implemented promptly. It is the responsibility of the site investigators to use continuous vigilance to identify and report protocol deviations and violations. All deviations and violations must be documented in source documents and reported to the OUCRU CTU within two days of being identified. In addition, protocol violations must be reported to the relevant ethics committees.

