### Study design

The study will start with a 10-patient prospective observational pilot study following the same entry and exclusion criteria as for the randomized trial and undergoing the same procedures. All 10 participants will receive chloroquine at the doses used in the trial; they will not be randomized. The purpose of the pilot study is to develop the study procedures for the randomized controlled trial, including the safe monitoring of participants, and to acquire some preliminary data on the safety of chloroquine in those with COVID-19 in Vietnam. Data from these patients will not be included in the final analysis. Once the pilot study has been completed, and the data reviewed by the trial steering committee (TSC), the data monitoring committee (DMC), and the Ministry of Health (MoH) ethics committee (EC), we will proceed with the trial. We aim for minimum delay between completing the pilot study and starting the randomized trial.

The main study is an open label, randomised, controlled trial with two parallel arms of standard of care (control arm) versus standard of care with 10 days of chloroquine (intervention arm) with a loading dose over the first 24 hours, followed by 300mg base orally once daily for nine days. The study will recruit patients in three sites in Ho Chi Minh City, Vietnam: the Hospital for Tropical Diseases (HTD), the Cu Chi Field Hospital, and the Can Gio COVID hospital. Additional sites including the National Hospital for Tropical Diseases in Ha Noi, Vietnam will be added based on enrolment rates.

All adult patients (≥18 years old) presenting to the study centres with positive throat/nose swabs (RT-PCR) for SARS-CoV-2 and requiring hospital admission will be eligible for study inclusion subject to the inclusion and exclusion criteria. Randomization will be stratified by severity of illness with severe disease being defined by a SpO2 ≤94%, or tachypnea (respiratory rate ≥24 breaths/min), and mild-moderate disease being defined by SpO2 >94% and respiratory rate <24 breaths/min without supplemental oxygen.

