If a participant chooses to discontinue their trial treatment (chloroquine), they should always be followed up (providing they are willing) and they should be encouraged not to leave the whole trial. If they do not wish to remain in trial follow-up, however, their decision must be respected and the participant will be withdrawn from the trial. The reason for the participant withdrawing should be ascertained wherever possible. Prior to withdrawing from the trial, the participant will be asked to have assessments performed as appropriate for the final visit although they would be at liberty to refuse any or all components of the assessment.

If a participant withdraws from the trial, the medical data collected during their previous consented participation in the trial will be kept and used in analysis. Consent for future use of stored samples already collected can be refused when leaving the trial early (but this should be discouraged and should follow a discussion). If consent for future use of stored samples already collected is refused, then all such samples will be destroyed following the policies of the institution where the samples reside at the time (local or central storage). Participants may change their minds about stopping trial follow-up at any time and re-consent to participation in the trial. Participants who stop trial follow-up early will not be replaced, as the total sample size includes adjustment for losses to follow-up.

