The frequency of serious and grade 3 and 4 ARs as well as the frequency of specific AEs will be summarized (both in terms of the total number of events as well as the number of participants with at least one event). The proportion of participants with at least one such event (overall and for each specific event separately) will be summarized and (informally) compared between the two treatment groups based on Fisher’s exact test if the expected number in one of the cells is at most one and the chi-square test if expected number in each cell is larger than one.

Analysis of other secondary outcomes

1. The duration of hospital stay from the time of randomization.2. The number of ventilator-free days during the first 28 days following randomization.3. The time to (all-cause) death following the first 10, 28, and 56 days since randomization.4. The WHO ordinal outcome scale for COVID-19 at days 28, 42 and 56
^24^.5. Fever clearance time.6. Development of ARDS defined by the Kigali criteria
^25^.7. Oxygenation-free days over the first 28 days.

The analyses of these secondary endpoints will be defined in the statistical analysis plan.

***Statistical hypotheses***. The primary null hypothesis is that the rate of clearance of virus from throat/nose swabs is not different between chloroquine compared with standard of care therapy.

***Analysis datasets***. The primary analysis population for all analysis is the full analysis population containing all randomized participants except for those mistakenly randomized without COVID-19. Participants will be analysed according to their randomized arm (intention-to-treat). In addition, the primary endpoint will be analysed on the per-protocol population, which will exclude the following participants: major protocol violations and those receiving less than one week of administration of chloroquine for reasons other than death.

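### Grade 1-2 adverse events are recorded by a rule that is not arm-neutral, so the informal between-arm comparison of specific AEs leans toward apparent harm from chloroquine wherever it includes them

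*Protocol article*

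**What the plan says.** **Recording.** Assessment of AEs (under Safety reporting) sets two rules. For severe or serious events there is no relatedness condition: "All grade 3 or 4, or SAEs and SARs, whether expected or not, should be recorded in the CRF". For the rest there is one: "Non-serious grade 1 or 2 AEs need not be recorded unless they are thought to be related to the trial treatment", or unless they lead to treatment being changed or interrupted.

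**What trial treatment means.** Discontinuation of treatment and participation (under Study procedures) glosses it: "If a participant chooses to discontinue their trial treatment (chloroquine), they should always be followed up". The Definitions text under Safety reporting uses the same gloss and adds the only mention of the other arm: "Reactions to the trial treatment (chloroquine) or comparator should be reported appropriately". Table 4 defines an AE as "Any untoward medical occurrence in a participant or clinical trial subject to whom an investigational medicinal product has been administered".

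**Design.** Study design describes an "open label, randomised, controlled trial with two parallel arms of standard of care (control arm) versus standard of care with 10 days of chloroquine".

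**Analysis.** The AEs paragraph of the Statistics section summarises serious and grade 3-4 ARs and, in addition, specific AEs, for which it gives no grade limit. The proportion of participants with at least one such event is to be reported as follows: "overall and for each specific event separately) will be summarized and (informally) compared between the two treatment groups". The test is Fisher's exact if an expected cell count is at most one, and chi-square otherwise. No significance level is stated.

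**The concern.** Whether a mild event has to be recorded depends partly on whether an unblinded investigator attributes it to chloroquine. That judgement can be made for a participant who takes chloroquine and cannot be made for one who does not. Nausea, vomiting, headache, diarrhoea and insomnia are on the article's list of expected toxicities, and they are also complaints that an ill inpatient in either arm may have. The same symptom can therefore enter the database from one arm and not from the other.

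A between-arm test on such counts partly measures the recording rule rather than the drug. What is at stake is the low-grade part of the safety description, which contributes to the secondary objective of defining chloroquine's safety profile. A later analysis plan cannot recover control-arm events that were never written down.

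**Working it through.** **1. Which analyses the rule touches.**

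| Analysis | Events used | Recording depends on relatedness? |
|---|---|---|
| Safety endpoints (Endpoints, Secondary endpoints) | SAEs; grade 3-4 AEs | No |
| Comparison named at the start of Safety reporting | Serious and grade 3-4 AEs | No |
| Interim DMC report | Mortality, SAEs, grade 3-4 AEs, viral clearance time | No |
| Comparison of specific AEs (Statistics, AEs) | No grade limit given | Yes, for grade 1-2 |

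Only the last row is exposed, together with any overall proportion that counts grade 1-2 events.

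**2. Inputs for the size.** The article gives no figure for low-grade AE rates or for how completely they are recorded, so there is no stated result to reproduce.
- Arm size: 240 randomised 1:1, so n = 120 per arm and N = 240 (Sample size calculation; Randomization and treatment allocation).
- Test: as stated in the AEs paragraph.
- Assumed: a 5% two-sided threshold, the true risk (equal in both arms), and the fraction of events recorded in each arm.

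**3. Formula.** Let x and y be the numbers of participants with the event recorded on chloroquine and control, and s = x + y. With equal arms the smallest expected count is s/2 (for s up to 120), so Fisher's test applies only when s ≤ 2. Otherwise

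chi-square = N(x − y)² / [s(N − s)], significant above 3.84.

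The probability of a false excess is the sum of the two binomial probabilities over all (x, y) with p < 0.05 and x > y, where x ~ Bin(120, risk × fraction recorded on chloroquine) and y ~ Bin(120, risk × fraction recorded in control).

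**4. One case by hand.** Take a true risk of 10%, with half recorded on chloroquine and none in control. Then x ~ Bin(120, 0.05), y = 0, and 6 v 0 are expected. The statistic reduces to 240x/(240 − x):
- x = 3: 720/237 = 3.04, not significant.
- x = 4: 960/236 = 4.07, significant.

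So the answer is P(x ≥ 4) = 1 − (0.0021 + 0.0134 + 0.0420 + 0.0869) = 0.856.

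**5. Range, by exact enumeration, with no true difference.**

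| True risk | Recorded, chloroquine v control | Expected recorded | False excess on chloroquine |
|---|---|---|---|
| 10% | 50% v 0% | 6 v 0 | 86% |
| 10% | 50% v 10% | 6 v 1.2 | 44% |
| 10% | 50% v 25% | 6 v 3 | 15% |
| 10% | 25% v 0% | 3 v 0 | 35% |
| 5% | 50% v 0% | 3 v 0 | 35% |
| 5% | 25% v 0% | 1.5 v 0 | 6% |
| 20% | 50% v 0% | 12 v 0 | 99.8% |
| 20% | 50% v 25% | 12 v 6 | 32% |
| 5-30% | equal, complete | equal | 2.4-2.6% |

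With equal recording the test is significant in either direction in 4.8-5.2% of trials, close to nominal. The excess in the other rows therefore comes from unequal recording.

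**The case against.** The strongest case on the other side has four parts.

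- **The main safety analyses are sound.** The safety endpoints and the DMC reports use SAEs and grade 3-4 AEs, recorded without regard to relatedness. This stands in full. A reader might infer that the safety-profile objective as a whole would be answered with an artefact. The documents do not support that, because the named safety endpoints do not use grade 1-2 events.
- **Control recording need not be zero.** The rule says such events need not be recorded; it does not forbid it. The second trigger refers to treatment in general and could be met by a change to standard of care. Reactions to the comparator are to be reported, laboratory abnormalities are recorded when any current treatment is altered, and Table 3 schedules AE evaluation without distinction by arm. This also stands. A reader might infer that low-grade control events are never captured, and so take 86% as the expected result, but that is the worst case for its row of assumptions. None of these routes makes recording equal, however: an untreated background symptom in a control participant still meets neither trigger. Nor should Table 4's AE definition be pressed to mean that controls can have no AEs, since the article plainly intends AEs to be compared between arms.
- **Specific AEs may mean serious or grade 3-4 events only.** If so, the problem disappears. The sentence lists specific AEs in addition to the serious and grade 3-4 category and gives no such limit, so the wider reading is open. The AE analysis is set out in the article and is not among the seven outcomes it leaves to the analysis plan.
- **The comparison is informal.** True: no significance level is stated and no formal error rate is breached. An informal p-value on unequally collected counts can still mislead.

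**Conclusion.** The point holds in limited form. The recording rule for non-serious grade 1-2 events is not arm-neutral, and the Statistics text allows those events into a between-arm test. Provided recording is more complete on chloroquine, which the rule makes likely, the bias is toward apparent harm.

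The size cannot be fixed from the documents. At a true risk of 10% with half of chloroquine-arm events recorded, it runs from 86% down to 15% as control recording rises from 0% to 25%, against about 2.5% with equal recording. At a 5% risk with only a quarter recorded on chloroquine and none in control it is 6%. These figures assume 120 per arm and a 5% threshold that the article does not state.

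A reader might go further and say that false harm signals must follow. That is firmer than the text allows, because background rates, attribution and control recording are all unknown. This is a correctable flaw in an informal secondary comparison.

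**What to change.** In the AEs paragraph of the Statistics section, limit the between-arm comparison, both overall and by specific event, to serious and grade 3-4 AEs. This matches what the opening of Safety reporting already says. The wording should be AEs and not ARs, as that paragraph now has it for the grade 3-4 category: a reaction to chloroquine cannot arise in a participant who does not receive it, so keeping ARs would bring the relatedness condition back. Describe grade 1-2 events in the chloroquine arm only, as tolerability, without a p-value. The cost is wording.

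If a low-grade comparison is wanted, record a short fixed list of symptoms identically in both arms, regardless of relatedness, at the AE evaluations already scheduled in Table 3. The cost is a few extra CRF items at visits already planned. Study status reports two participants enrolled, and the trial opens with a 10-patient pilot whose data stay out of the final analysis, so at that stage either change could still be made.

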***Secondary endpoints***

The duration of hospital stay from the time of randomization.The number of ventilator-free days during the first 28 days following randomization.The time to (all-cause) death following the first 10, 28, and 56 days since randomization.The WHO ordinal outcome scale for COVID-19 at days 28, 42 and 56
^24^.Fever clearance time (defined as temperature <37.5°C for 48 hours).Development of acute respiratory distress syndrome (ARDS) defined by the Kigali criteria
^25^.Oxygenation-free days over the first 28 days.Risk of serious adverse events (SAEs).Risk of grade 3 or 4 adverse events (AEs).

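### The intervention test for laboratory abnormalities narrows the rule that all grade 3 or 4 events are recorded, and gives chloroquine patients one more route to mandatory recording than controls

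*Protocol article*

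**What the plan says.** Three statements in the protocol article's Safety reporting section govern a laboratory result.

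- General recording rule (Assessment of AEs): "All grade 3 or 4, or SAEs and SARs, whether expected or not, should be recorded in the CRF".
- Laboratory rule, shortly after: "A laboratory abnormality must be recorded as a clinical AE only if it is associated with an intervention". The term is then defined by an open list: "Intervention includes, but is not limited to, discontinuation of a current treatment, dose reduction/delay of a current treatment, or initiation of a specific treatment".
- Discretionary route: "any medically important laboratory abnormality may be reported as an AE at the discretion of the investigator". Its scope is explained: "This would include a laboratory result for which no intervention is needed, but the abnormal value suggests a disease or organ toxicity".

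The paragraph closes with "Laboratory events will be graded according to CTCAE definitions".

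The count is used in three places. The risk of grade 3 or 4 AEs is listed under Secondary endpoints. The opening of Safety reporting says these events will be compared between arms. The interim reports to the DMC summarise them by arm. The AE paragraph under Statistics describes an informal comparison by Fisher's exact or chi-square test. Study design states that the trial is open label against standard of care, and no placebo is described.

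**The concern.** Whether a laboratory value must be recorded depends on a management decision taken after randomisation by staff who know the allocation. Two of the three listed examples of an intervention are changes to a treatment the patient is already receiving. A chloroquine patient has one such treatment more than a comparable control patient. Other things equal, the same ALT or neutrophil count has one more way of becoming a mandatory AE on chloroquine.

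There is a second problem, which does not depend on arm. A grade 3 or 4 value on which no one acted falls under mandatory recording by the general rule and outside it by the laboratory rule. Sites may resolve this differently, and some severe values may not be counted at all.

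Defining the safety profile is a secondary objective. The article lists neutropenia, agranulocytosis, thrombocytopenia and hepatitis among the known toxicities of chloroquine, with frequency unknown or rare. The scheduled blood counts and chemistry are the tests that would show them.

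**Working it through.** The plan gives no figure on this point, so there is nothing to reproduce. The check sets the rules side by side and then illustrates how large the effect could be.

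**The rules applied to one grade 3 or 4 laboratory value**

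| What was done | General rule | Laboratory rule, chloroquine | Laboratory rule, control |
|---|---|---|---|
| Nothing | record | discretionary | discretionary |
| Another current treatment stopped, reduced or delayed | record | mandatory | mandatory |
| Specific treatment started | record | mandatory | mandatory |
| Chloroquine stopped, reduced or delayed | record | mandatory | cannot occur |

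The first row shows the conflict between the rules. The last row shows the asymmetry. All other rows are the same in both arms.

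**Illustration of size**

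Inputs from the protocol: 240 patients (Sample size calculation) allocated 1:1 (Randomization and treatment allocation), so 120 per arm.

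Assumed inputs, because the document gives none:
- *p*, the true proportion with a grade 3 or 4 laboratory value, equal in both arms;
- *c*, the probability that such a value is counted in control;
- *e*, the probability that a value otherwise uncounted is counted because chloroquine was stopped, reduced or delayed.

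Formulas:
- capture on chloroquine = *c* + (1 − *c*) × *e*
- apparent ratio = [*c* + (1 − *c*) × *e*] / *c*
- extra counted chloroquine patients = 120 × *p* × (1 − *c*) × *e*

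Example: with *c* = 0.3 and *e* = 0.4, capture is 0.3 + 0.7 × 0.4 = 0.58 and the ratio is 0.58 / 0.30 = 1.93. With *p* = 10%, the extra count is 120 × 0.10 × 0.28 = 3.4.

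The last column is the exact binomial probability of a nominally significant result with chloroquine worse. It uses the protocol's switch between Fisher and chi-square, and a two-sided 0.05 level, which is assumed. All rows use *p* = 10%.

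| *c* | *e* | Capture on chloroquine | Apparent ratio | Extra per 120 | Chance of "worse" |
|---|---|---|---|---|---|
| 0.5 | 0 | 0.50 | 1.00 | 0.0 | 2.4% |
| 0.5 | 0.1 | 0.55 | 1.10 | 0.6 | 3.6% |
| 0.5 | 0.2 | 0.60 | 1.20 | 1.2 | 5.2% |
| 0.5 | 0.4 | 0.70 | 1.40 | 2.4 | 9.6% |
| 0.3 | 0.4 | 0.58 | 1.93 | 3.4 | 16.9% |

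The ratio does not depend on *p*. Over the same four non-zero scenarios, the last column runs from 2.9% to 9.6% at *p* = 5%, and from 4.5% to 34.6% at *p* = 20%.

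If every value is counted whatever was done, *c* = 1, the term in *e* vanishes and the expected ratio is 1.00.

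**The case against.** A reader might infer that a laboratory result counts only if it led to an intervention, so that control patients have practically no way in. The text does not support that. It says associated with, not led to, and it fixes only when recording is mandatory. The list of interventions is open and refers to any current treatment. Control patients are inpatients on standard of care who may have a drug stopped or a treatment started. A medically important value may also be reported without any intervention in either arm, and that clause is aimed at results suggesting organ toxicity. All of this stands and makes the asymmetry smaller. It does not remove it, because the shared routes exist in both arms, the chloroquine route exists in one, and the discretionary route is optional and unblinded.

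The mechanism also rests partly on assumption. The stopping and interruption rules under Study intervention concern arrhythmia, syncope and QTc, not ALT or blood counts. The discontinuation section lets the investigator stop for an AE, but nothing shows how often a laboratory value would prompt it. This stands, and it is why no size can be claimed.

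The two recording rules might be harmonised by reading laboratory events as graded and recorded in their own right, separately from clinical AEs. That reading is possible, but the text does not state it, and a site could reasonably follow the narrower one.

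Finally, tabulating laboratory values by grade could sit in the analysis plan, which is not shown, and the DMC can ask for further safety analyses. The absence of such a table is therefore not a fault. The recording rule, however, is written in this document and contradicts its neighbour.

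**Conclusion.** The point holds in a limited form. The general rule and the laboratory rule conflict for grade 3 or 4 values with no action taken, and such values may be missed in either arm. The same value has one additional route to mandatory recording on chloroquine, in an open-label trial where the count is a between-arm safety endpoint and feeds DMC decisions.

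The likely direction is against chloroquine, other things equal, though unblinded discretion could offset it. The size is not derivable from the document. With control capture of 30-50% and an added chance of 10-40% on chloroquine, all assumed, the apparent ratio runs from 1.10 to 1.93 when the truth is 1.

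Much larger distortions should not be inferred. Capture of 90% against 20% would give 0.9 / 0.2 = 4.5, but it requires *e* = (0.9 − 0.2) / (1 − 0.2) = 0.875. Chloroquine would have to be interrupted for nearly nine in ten values that would otherwise go uncounted, and nothing in the protocol supports that.

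**What to change.** Reconcile the two rules under Assessment of AEs so that the intervention test applies only to grade 1-2 laboratory results, and state that every grade 3 or 4 laboratory value is recorded whatever was done.

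For the grade 3 or 4 endpoint and the DMC tables, derive laboratory events from the blood count and chemistry results that Table 3 schedules with no distinction by arm. Grade them by CTCAE in the database, and show them alongside the investigator-reported AEs. Use the scheduled values for this table, because extra tests ordered at the bedside could again differ by arm.

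The cost is one reworded sentence and a short derivation program, with no new tests or visits. Laboratory event counts will be higher in both arms. Study status reports two participants enrolled, so the change can apply almost from the start.
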